## Background

Proximal femoral fractures are amongst the most common fractures in the elderly [1] with the incidence rate increasing with age. In the Netherlands 20,000 patients are admitted with a proximal femoral fracture to the hospital each year [2, 3]. This number is expected to rise because of our ageing society. Approximately 20% live in a nursing home prior to the fracture. Proximal femoral fractures result in activities of daily living (ADL) dependence and increased morbidity, strongly diminishes the patients’ (health-related) Quality of Life (QoL) and total health care costs [4–7].

A proximal femoral fracture is also strongly associated with mortality. Over 30% of patients die within the first year and 8–13.3% die within the first month [8–10]. Mortality is highest among elderly with both physical and cognitive comorbidities [9, 10]. A 36 and 55% mortality rate within 6 months after fracture has been reported for institutionalized patients and patients with advanced dementia, respectively [11, 12]. This shows that the hip fracture is merely a symptom of the frail status of these patients and the start of cascade breakdown at the end of life.

Operative treatment allows early mobilization, is effective in pain relief, and is believed to prevent secondary complications like pneumonia, urinary tract infection, and pressure sores. However, surgery will not prevent frail patients from developing aforementioned complications. Instead, patients may develop additional surgical complications like bleeding, infection, and non-union, necessitating further (operative) interventions [13]. Hospital admission after a proximal femoral fracture itself can provoke cognitive impairment or delirium in these patients who often live in delicate equipoise in an institutionalized setting.

Although surgery is considered a good analgesic option, it is not the only analgesic option. Moreover, surgery also has disadvantages. It is questionable whether surgery is beneficial in terms of quality of life and whether surgery is satisfactory for family and caretakers involved. The World Health Organization (WHO) definition for palliative care supports a holistic approach in facing life-threatening illness, which is a proximal femoral fracture in a frail elderly patient. Randomized trials comparing operative and nonoperative management in institutionalized elderly are scarce, due to ethical issues, and focus on mortality instead of quality of life.

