### Statistical analysis

Data will be analyzed using the Statistical Package for the Social Sciences (SPSS) version 24.0 or higher (SPSS, Chicago, Ill., USA) and will be reported following the STrengthening the Reporting of OBservational studies in Epidemiology (STROBE) guidelines. Normality of continuous data will be tested with the Shapiro-Wilk test. Homogeneity of variances will be tested using the Levene’s test. A two-sided *p*-value < 0.05 will be taken as threshold of statistical significance in all statistical tests. The analysis will be performed on a per-protocol basis, (as that is the most conservative approach) and verified by an intention-to-treat analysis if needed. Patients who have died will remain in the analysis as censored. If necessary, missing values will be replaced using multiple imputation following the predictive mean matching method, using ten imputations.

Descriptive analysis will be performed in order to report the outcome measures and other variables collected for the entire population as well as per treatment group. Continuous data will be reported as mean and SD (if Normal) or median and quartiles (if non-Normal), categorical data as number with percentage.

Univariate comparison between the groups will be done using Student’s T or Mann-Whitney U-test (for Normal and non-Normal data, respectively), or Chi-squared test or Fisher’s Exact test (categorical data, as applicable). The Student’s T-test will be done with equal variance assumed or not assumed, based upon the results of the Levene’s test.

For the primary outcome measure, a non-inferiority margin of 0.15 points for mean EQ-5D scores was chosen because it is reasonable and on the border of what would be considered a clinically important effect. The null hypothesis in the non-inferiority framework is that nonoperative management is inferior to operative management with regards to the EQ-5D score. This hypothesis will be tested through the adjusted contrast between the two interventions at 6 months. Specifically, the 95% confidence interval of the estimated contrast will be examined, and if the limit of the interval is less than the threshold value of 0.15 points, non-inferiority of nonoperative management to operative management at 6 months will be concluded.

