### Sample size calculation

The sample size calculation is based on a non-inferiority design, i.e., on the hypothesis that nonoperative management is non-inferior to operative management. As stated before the EQ-5D will serve as primary outcome measure. We have used the results from earlier studies on proximal femoral fracture treatment in the elderly for the sample size calculation [51–53]. Assuming a two-sided significance level (alpha) of 0.05 and a power of 80% with a standard deviation (s) of 0.30 on the EQ-5D utility score and a noninferiority limit (d) of 0.15 (which equals 0.5 SD), a total of 50 subjects are needed in each treatment arm. Taking into account a rate of 60% loss to follow-up and mortality until 3 months, a total number of 160 participants has to be recruited.

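### Ten imputations are few for the attrition this plan expects: if the 6-month contrast comes from imputed data, a borderline non-inferiority verdict may depend on the random seed (minor, free to improve)

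*Protocol article*

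**What the plan says.** Three statements in the protocol article bear on this point.

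- **Imputation (Statistical analysis).** Where needed, "missing values will be replaced using multiple imputation following the predictive mean matching method, using ten imputations". The number is fixed but the use of imputation is conditional. On deaths, the same paragraph says: "Patients who have died will remain in the analysis as censored".
- **Decision rule (Statistical analysis).** The adjusted contrast at 6 months is judged by its 95% confidence interval: "if the limit of the interval is less than the threshold value of 0.15 points, non-inferiority of nonoperative management to operative management at 6 months" is concluded. The primary model is a GEE on the repeated EQ-5D scores.
- **Expected attrition (Sample size calculation).** "Taking into account a rate of 60% loss to follow-up and mortality until 3 months, a total number of 160 participants has to be recruited". Loss and death are given as one figure. The Background supplies mortality separately: "A 36 and 55% mortality rate within 6 months after fracture has been reported for institutionalized patients and patients with advanced dementia, respectively".

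**The concern.** Multiple imputation involves random draws. With few imputations and much missing information, the pooled estimate and its confidence limit change when the draws are repeated on the same data. Usually this is harmless. Here a single limit is compared with a fixed threshold, the sample is small, and the plan itself expects heavy attrition. If the limit lands near 0.15, a repeat with another seed could reverse the reported conclusion although no patient's data have changed. The number of imputations is a stated choice in the article, not a detail left to another document, and a larger number would remove most of the effect.

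**Working it through.** **1. The plan's own figures.** With SD 0.30 and margin 0.15, n per arm = 2 × 0.30² × (z_α + z_β)² / 0.15².

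- One-sided 0.05: 8 × (1.645 + 0.842)² = 49.5, so 50 per arm, as stated.
- Two-sided 0.05, which matches the 95% interval: 8 × (1.960 + 0.842)² = 62.8, so 63 per arm.
- The total of 160 is 100 × 1.60. A 60% loss from 160 leaves 160 × 0.40 = 64 observed, not 100.

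The sample size is a separate matter. It enters here only because the section can be read as leaving either 64 or 100 patients with data.

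**2. Share of living patients to impute.** The 60% has to be split by assumption. Deaths are taken as not imputed.

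- *Constant hazard, 64 observed.* Three-month survival is √(1 − 0.36) = 0.80 or √(1 − 0.55) = 0.67, so 128 or 107 of 160 are alive. The missing share is (128 − 64)/128 = 50% or (107 − 64)/107 = 40%.
- *All 6-month deaths before 3 months, 64 observed.* (0.60 − 0.36)/0.64 = 37.5%, or (0.60 − 0.55)/0.45 = 11%.
- *100 observed, as the total of 160 implies, with the constant-hazard survivors.* (128 − 100)/128 = 22%, or (107 − 100)/107 = 7%.

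The range is therefore about 7% to 50%.

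**3. Seed effect on the limit.** Assumptions: SD 0.30, equal arms, no true difference, no covariates, and a fraction of missing information λ equal to the share missing. With n living patients per arm, the within-imputation variance is U = 2 × 0.30²/n and the between-imputation variance is B = U × λ/(1 − λ). The pooled estimate varies between seeds with SD √(B/m). At λ = 0.375, n = 51.2, so U = 0.00352 and B = 0.00211, and with m = 10 the SD is √0.000211 = 0.0145. The limit varies more, because B is itself estimated from m draws and also sets the degrees of freedom.

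I simulated the limit with Rubin's rules and Barnard-Rubin degrees of freedom, analysing each trial twice with independent draws (100,000 trials per row). The lower 95% limit of nonoperative minus operative was compared with −0.15.

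| Observed | Missing among living | Seed SD of limit, m = 10 | Opposite verdicts, m = 10 | Seed SD of limit, m = 100 | Opposite verdicts, m = 100 |
|---|---|---|---|---|---|
| 100 | 7% | 0.005 | 3.7% | 0.002 | 1.1% |
| 100 | 22% | 0.012 | 7.6% | 0.003 | 2.2% |
| 64 | 11% | 0.009 | 5.4% | 0.003 | 1.7% |
| 64 | 37.5% | 0.022 | 12.8% | 0.006 | 3.8% |
| 64 | 40% | 0.023 | 13.3% | 0.007 | 3.9% |
| 64 | 50% | 0.028 | 15.8% | 0.008 | 4.7% |

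Against the margin, 0.0054/0.15 = 4% and 0.028/0.15 = 19%.

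**4. Cross-check with predictive mean matching itself.** A second simulation imputed from two earlier EQ-5D values (assumed correlation 0.5 between visits). At 40% and 50% missing with ten imputations, the seed SD of the limit was 0.017 to 0.021 and verdicts disagreed in 10.8% and 13.3% of trials. With 100 imputations the disagreement was 3.2% and 3.6%. Earlier visits lower the missing information, so these figures are somewhat smaller than those in the table.

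**5. Average power.** In the table's worst row, non-inferiority is concluded in 46% of trials with ten imputations and in 49% with 100. In the 7% row the figures are 69% and 70%.

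**The case against.** The strongest objection is that the deciding limit need not come from imputed data at all. Imputation is conditional, the primary model is a GEE that can use the available visits, and nothing in the article ties the imputations to the 6-month contrast. Without imputation there is no seed. This stands, and it makes the point conditional. It does not remove it: a standard unweighted GEE on available visits generally needs data missing completely at random, which is hard to defend in frail patients, so the condition may well be met.

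The size also depends on the split of the 60%. A reader might infer that 60% of the data would be imputed. The article does not support that, because the figure includes deaths, and those patients are kept as censored. Even the 40% to 50% cases rest on a constant hazard. The Background reports 8% to 13.3% mortality in the first month against just over 30% in a year, whereas a constant hazard at 30% a year gives about 3% a month. Earlier deaths mean fewer living patients with missing scores, and reading the total of 160 as leaving 100 evaluable lowers the share further. This objection stands too, and is why a range is given.

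The disagreement rates also partly reflect small numbers. With 64 observed, the standard error is about 0.075 and the typical limit under no difference lies almost on the margin, so any noise matters. A larger sample would reduce the problem.

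Finally, a recorded seed and Monte Carlo error reporting are ordinary SAP detail, and their absence from the article is no defect. The number ten, however, is stated.

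**Conclusion.** The point holds as a minor, conditional one. If the 6-month contrast is estimated from ten imputed data sets, the seed moves the deciding limit with an SD of about 0.005 to 0.028, and two seeds give opposite verdicts in about 4% to 16% of trials; 100 imputations bring this to about 1% to 5%. These figures assume 7% to 50% of living patients imputed, equal arms, SD 0.30, no true difference, and missing information equal to the share missing. They use 3-month attrition, although the decision is at 6 months, when losses may be larger.

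Two stronger readings should be resisted. A reader might infer that ten imputations make the analysis invalid. They do not: Rubin's rules allow for a finite number of imputations, there is no bias, and average power falls by only about 4 percentage points even at the top of the range. A reader might also infer that any two analysts following the plan risk opposite conclusions. That applies only if both impute for the primary contrast and the limit falls close to 0.15. What is lost is the reproducibility of a borderline verdict.

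**What to change.** In the Statistical analysis section, change the number of imputations from ten to at least 100, with a fixed and recorded seed, and report the Monte Carlo error of the 6-month confidence limit that decides non-inferiority. The seed and the error report may equally stand in the SAP. The only cost is computing time; no patients, visits or data are added.

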### Study design and setting

This study will be a two-arm non-randomized (observational) multicenter cohort study and an economic evaluation alongside. The study will be conducted with a non-inferior design. Relevant societies for surgery (Dutch Association of Surgery (NVvH), Dutch Association of Trauma Surgery (NVT), Dutch Orthopaedic Association (NOV), and Dutch Association of Orthopaedic Surgery (NVOT)), clinical geriatrics (Dutch Association of Clinical Geriatrics (NVKG)), elderly care (Association of Elderly Care Physicians (VERENSO)), the Dutch Patient Federation, and two committee members of the Dutch guideline for treatment of proximal femoral fractures are represented in the study team. Patients will be recruited from several hospitals throughout The Netherlands. The following 26 hospitals will participate: Albert Schweitzer Ziekenhuis, Alrijne Ziekenhuis, Amphia Ziekenhuis, Amsterdam UMC (location VUmc), Bernhoven, Catharina Ziekenhuis, Deventer Ziekenhuis, Dijklander Ziekenhuis (location Westfriesgasthuis), Dijklander Ziekenhuis (location Waterland Ziekenhuis), Elisabeth TweeSteden Ziekenhuis, Erasmus MC, Flevo Ziekenhuis, Isala, Maasstad Ziekenhuis, Meander MC, Noordwest Ziekenhuisgroep, OLVG, Radboud UMC, Rijnstate, Rode Kruis Ziekenhuis, St. Antonius Ziekenhuis, Streekziekenhuis Koningin Beatrix, Tergooi, Ziekenhuis Gelderse Vallei, Ziekenhuis Tjongerschans, and Zorggroep Twente.

The study has started in September 2018. The recruitment period will be 24 months, with a follow-up of 6 months. The results of the study are expected mid-2021.

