Multivariable analysis for continuous outcome measures that are repeatedly measured over time will be done using generalized estimating equations (GEE) for longitudinal analysis on a per-protocol and intention-to-treat basis to investigate the effect of treatment. In the primary GEE model, the primary outcome variable studied (quality of life on EQ-5D) will be analyzed as a dependent variable, using treatment (nonoperative versus operative) as between subjects variable and time as within subjects variable. The interaction term of group and time (group x time) will be assessed, to evaluate whether the change over time differed between groups. Analyses will be corrected for baseline differences and all models will be corrected for center of inclusion. Repeatedly measured continuous secondary outcome variables will be analyzed using similar GEE models. Continuous outcome measures only ones and dichotomous secondary outcome measures will be analyzed using multivariable linear regression models and logistic regression models, respectively.

Subgroup analysis are planned for patients with an intracapsular or extracapsular fracture.

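### Letting Levene's test choose the t-test can misstate the 5% level of unadjusted comparisons if arm sizes and SDs both differ; the unequal-variance test should be used without the pretest (minor)

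*Protocol article*

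**What the plan says.** The Statistical analysis section sets out a chain of preliminary tests. "Normality of continuous data will be tested with the Shapiro-Wilk test", and homogeneity of variances is checked with Levene's test. "Univariate comparison between the groups will be done using" Student's t-test for Normal data and Mann-Whitney for non-Normal data. For the t-test branch, the "T-test will be done with equal variance assumed or not assumed, based upon the results of the" Levene test. A two-sided p-value below 0.05 "will be taken as threshold of statistical significance in all statistical tests".

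The non-inferiority question is handled elsewhere: "This hypothesis will be tested through the adjusted contrast between the two interventions at 6 months". The primary model is a GEE, and "Analyses will be corrected for baseline differences and all models will be corrected for center of inclusion".

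The design is a "two-arm non-randomized (observational) multicenter cohort study". The section on the shared decision process leaves the choice of arm to that process, so nothing fixes the arm sizes. The sample size section nonetheless counts on 50 per arm, with one common SD of 0.30.

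**The concern.** The pooled t-test is safe against unequal variances when the arms are equal in size, and against unequal arms when the variances are equal. It fails when both differ. A preliminary variance test is meant to guard against that, but with a small arm it has little power. It therefore often keeps the pooled test in the situation where that test is wrong.

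At stake is whether the nominal 5% holds for the unadjusted between-arm comparisons of continuous variables. The error is too high when the smaller arm is the more variable one and too low when it is the less variable one. The rule is written out in the article, so this concerns a stated choice and not an omission.

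**Working it through.** The plan gives no error rate for this rule, so there is no figure of its own to reproduce.

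**Inputs from the protocol article.** Total 160 and 60% loss and mortality until 3 months (Sample size calculation); common SD 0.30 (same section); 20.3% nonoperative in earlier cohorts and over 90% operated in practice (Background); two-sided 0.05 (Statistical analysis).

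**Arm sizes to examine.**
- About 20% nonoperative: 160 × 0.2 = 32 v 128.
- 10% nonoperative: 160 × 0.1 = 16 v 144.
- After 60% loss: 160 × 0.4 = 64. Then 64 × 0.2 ≈ 13 v 51, and 64 × 0.1 ≈ 6 v 58.
- Equal arms for reference: 80 v 80 and 50 v 50.

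**Assumption.** The article gives no SD by arm. The ratio of the smaller arm's SD to the larger arm's SD was varied from 0.67 to 1.5.

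**Why the pooled test fails.** The true variance of the difference is s₁²/n₁ + s₂²/n₂. The pooled test uses sₚ²(1/n₁ + 1/n₂), with sₚ² = [(n₁−1)s₁² + (n₂−1)s₂²]/(n₁+n₂−2).

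For 13 v 51 with SDs 0.45 and 0.30:
- True: 0.2025/13 + 0.09/51 = 0.01734, SE 0.132.
- Pooled: sₚ² = (12 × 0.2025 + 50 × 0.09)/62 = 0.1118; times (1/13 + 1/51) = 0.0965 gives 0.01079, SE 0.104.
- The pooled SE is about 21% too small (0.104/0.132 = 0.79).

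With the SDs swapped:
- True: 0.09/13 + 0.2025/51 = 0.01089, SE 0.104.
- Pooled: 0.1807 × 0.0965 = 0.01745, SE 0.132, about 27% too large.

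With n₁ = n₂ = n both formulas give (s₁² + s₂²)/n, which is why equal arms show no problem.

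**Type I error by simulation.** Normal data, equal means, 40,000 replicates per scenario, mean-centred Levene at 0.05 choosing pooled or Welch. The Monte Carlo standard error near 5% is √(0.05 × 0.95/40,000) ≈ 0.1 point. The ratio columns give the Levene-gated test in %; the last column is the range for Welch always used.

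| Arms | 0.67 | 0.77 | 1.0 | 1.2 | 1.3 | 1.5 | Welch |
|---|---|---|---|---|---|---|---|
| 80 v 80 | 4.9 | 4.9 | 5.1 | 4.9 | 4.9 | 4.9 | 4.9–5.1 |
| 50 v 50 | 4.9 | 4.9 | 5.2 | 4.9 | 4.9 | 5.0 | 4.9–5.2 |
| 32 v 128 | 4.4 | 3.9 | 5.2 | 6.8 | 6.9 | 6.3 | 4.9–5.1 |
| 16 v 144 | 3.7 | 3.3 | 5.3 | 8.1 | 8.7 | 8.6 | 4.9–5.2 |
| 13 v 51 | 3.4 | 3.5 | 5.2 | 7.0 | 7.7 | 8.3 | 4.9–5.1 |
| 6 v 58 | 3.0 | 3.2 | 5.9 | 8.6 | 10.4 | 12.2 | 5.3–5.6 |

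A repeat with 20,000 replicates agrees: 8.4% and 3.6% at 13 v 51 for ratios 1.5 and 0.67, and 8.7% and 3.7% at 16 v 144.

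**How often Levene's test catches the difference.** At ratio 1.3: 43% of runs (32 v 128), 28% (16 v 144), 22% (13 v 51), 14% (6 v 58). At ratio 1.5: 77%, 55%, 42%, 26%. A large difference is caught more reliably: at ratio 2 the gated error at 32 v 128 is back to 5.1%.

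**Cost of always using Welch.** Power of the two-sided test for a difference of 0.15 with both SDs 0.30, gated v Welch: 32 v 128, 70.8% v 69.7% (1.1 points); 13 v 51, 35.3% v 33.1% (2.2); 16 v 144, 46.9% v 43.7% (3.2); 6 v 58, 21.6% v 17.5% (4.0). With 80 v 80 or 50 v 50 there is no loss.

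**The case against.** Several points on the other side stand and set the size of this one.

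- **Scope.** No planned treatment-effect conclusion rests on the gated test. Non-inferiority uses the adjusted contrast, repeated secondary outcomes use GEE, and continuous outcomes measured once have multivariable linear regression. The unadjusted tests are also confounded by treatment choice, as the Discussion concedes, and that limits them more than a shift of a few points in type I error.
- **Unequal arms alone do no harm.** A reader might infer that imbalance makes these p-values wrong. With equal SDs the gated test runs at 5.2% to 5.3% in the unbalanced scenarios, apart from 5.9% at 6 v 58. The article gives one common SD and no evidence of a difference. Unequal spread is plausible, because the Discussion expects that nonoperative patients may be in worse condition, but it is not shown.
- **Imbalance is inferred, not planned.** The calculation assumes 50 per arm, and a more structured decision process could move the nonoperative share away from the historical figures. At a milder 20 v 44 the gated error peaks at about 6.6%. The 12% figure combines a 10% share, the full 60% loss and an SD ratio of 1.5.
- **The simulation covers the t-test branch only.** It uses Normal data and omits the Shapiro-Wilk step, so it says nothing about outcomes sent to Mann-Whitney.
- **Welch is not free or exact everywhere**, as the power losses and the 5.6% at 6 v 58 show.

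A second tempting reading is that the Shapiro-Wilk step undermines the primary conclusion, because a rank p-value cannot be set against a margin on the mean. It is true that "a non-inferiority margin of 0.15 points for mean EQ-5D scores was chosen", but the plan reads that margin against the 95% confidence interval of the adjusted contrast and never against a rank test. Costs and QALYs are analysed with multilevel models and bootstrapping. That argument has no support in the text.

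**Conclusion.** The point holds as a minor one. The stated rule does not secure its 5% level when arm sizes and SDs differ together. For SD ratios of 0.67 to 1.5 and at least 13 patients in the smaller arm, the error is roughly 3.5% to 9% (lowest and highest simulated values 3.3% and 8.7%). At 6 v 58 it ranges from 3.0% to 12.2%. Welch without a pretest stays within 4.9% to 5.2% in the same unbalanced scenarios, and within 5.3% to 5.6% at 6 v 58.

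This rests on two assumptions that the article makes plausible but does not establish: that the arms will be clearly unequal, and that their SDs will differ. It reaches only unadjusted univariate t-tests. The primary non-inferiority conclusion, the adjusted secondary analyses and the economic evaluation do not depend on it.

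**What to change.** In the Statistical analysis section, remove the use of Levene's test to select the t-test, and state that all univariate t-test comparisons will use the unequal-variance (Welch) version. The planned analysis already allows for this version, so no new method or data are needed; the edit is one sentence. The price is the 1 to 4 points of power shown above at 20/80 to 10/90 splits if the SDs turn out equal, and nothing if the arms are equal. No change to the margin, the GEE or the economic analysis follows from this point.

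### The non-inferiority test is at 6 months, but the sample size allows for loss and death only until 3 months, so the stated 80% power does not apply to the deciding contrast

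*Protocol article*

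**What the plan says.** Statistical analysis: the null hypothesis is that nonoperative management is inferior on the EQ-5D. "This hypothesis will be tested through the adjusted contrast between the two interventions at 6 months". Non-inferiority at 6 months is concluded "if the limit of the interval is less than the threshold value of 0.15 points", the interval being a 95% one.

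Sample size calculation: the calculation assumes two-sided alpha 0.05 and 80% power, "with a standard deviation (s) of 0.30 on the EQ-5D utility score and a noninferiority limit (d) of 0.15". It concludes that "a total of 50 subjects are needed in each treatment arm". The step to 160 recruited patients is described as "Taking into account a rate of 60% loss to follow-up and mortality until 3 months".

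The schedule of events lists 3 months and 6 months as separate visits. No figure for loss between them is given.

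Two other statements bear on the size of that loss. The Background reports: "A 36 and 55% mortality rate within 6 months after fracture has been reported for institutionalized patients and patients with advanced dementia, respectively". It also gives unadjusted pooled mortality odds ratios of 3.95 (30 days) and 3.84 (1 year) for nonoperative versus operative management.

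**The concern.** A power statement is useful only for the comparison that will be made, at the time it will be made. Here the test and the attrition allowance refer to visits three months apart, in patients chosen for limited life expectancy. Patients who die supply no 6-month EQ-5D, and the plan keeps them in the analysis as censored. Each loss between the two visits therefore reduces the information behind the deciding confidence interval, and none of it is budgeted.

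At stake is a study more likely than its stated power suggests to miss non-inferiority when the treatments are in fact equal. Because the results are meant to inform guidelines, such a failure could be read as evidence against nonoperative care. This is more than a detail that an analysis plan could supply later: the article states both time points, and they disagree.

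**Working it through.** **Inputs.** From the article: SD 0.30, margin 0.15, 50 evaluable per arm, 60% loss and mortality by 3 months, 160 recruited, 95% confidence interval rule (equivalent to one-sided 0.025). Assumed: true difference 0, equal arms, normal approximation, simple two-group comparison.

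**Reproducing the plan's figures.**
- Patients per arm: n = 2(z_alpha + z_beta)² × SD²/margin², with SD²/margin² = 4.
  - One-sided 0.05: 2 × (1.645 + 0.842)² × 4 = 49.5, so 50.
  - One-sided 0.025, which matches the stated alpha and interval: 2 × (1.960 + 0.842)² × 4 = 62.8, so 63.
  - The stated 50 is therefore a one-sided 0.05 figure. Under the 95% interval rule, 50 per arm gives 70.5% power.
- Inflation: 100 × 1.60 = 160 reproduces the stated total. Leaving 100 after 60% loss requires 100/(1 − 0.60) = 250.

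**Power at 6 months with 160 recruited.** Power = Phi(0.15/SE − z), with SE = 0.30 × sqrt(2/n) for n per arm. Loss by 6 months cannot be below loss by 3 months, so 60% is its minimum under the plan. The higher rates are assumptions.

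| Loss by 6 months | Left of 160 | Per arm | Power, one-sided 0.05 | Power, 95% CI rule |
|---|---|---|---|---|
| 60% (minimum) | 64 | 32 | 64% | 52% |
| 65% (assumed) | 56 | 28 | 59% | 46% |
| 70% (assumed) | 48 | 24 | 53% | 41% |

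The first row is also the 3-month position, so the fall to 52% is already present before the timing mismatch has any effect.

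**Isolating the timing mismatch.** Suppose the inflation were done correctly and 250 were recruited:
- 60% lost: 100 left, 50 per arm, power 70.5% under the 95% rule.
- 65% lost: 87.5 left, 43.75 per arm; SE = 0.30 × sqrt(2/43.75) = 0.0641; Phi(2.339 − 1.960) = 65%.
- 70% lost: 75 left, 37.5 per arm; SE = 0.30 × sqrt(2/37.5) = 0.0693; Phi(2.165 − 1.960) = 58%.

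The mismatch alone therefore costs about 6 to 12 points under these assumed rates.

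**By arm (illustration only).** Assume 80 recruited per arm and apply odds ratio 3.84 to all loss. A total loss of 60% leaves about 44 operative and 20 nonoperative patients; 70% leaves about 35 and 13. Against 50 per arm the total shortfall is mostly nonoperative. The additional loss between the two scenarios is about 10 operative and 6 nonoperative.

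**The case against.** The best defence is that the 60% is generous enough to cover 6 months as well. The Background's 36% six-month mortality for institutionalized patients would, with no other loss, leave about 102 of 160. Even if 36% is assigned to the operative arm and odds ratio 3.84 is added for the other (80 per arm), about 51 and 25 are alive at 6 months. That is roughly 52% attrition, inside the 60% allowance. With 125 per arm recruited, the same mortality leaves about 80 and 40 and gives 73% power under the 95% rule, slightly above the 70.5% from 50 per arm. On those figures the mismatch costs nothing.

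This stands as a limit on size. It does not remove the inconsistency: the article ties its 60% to 3 months, and cumulative loss cannot be lower at 6. If 60% was meant to reach 6 months, the article should say so.

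The planned generalized estimating equations model uses all visits, and multiple imputation is available, so some information may be recovered for living patients with missing questionnaires. Neither supplies an observed 6-month score for a patient who has died.

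Two stronger readings are tempting. A reader might attribute the whole fall from 80% to about 52% to the timing mismatch. That is wrong: most of it comes from the inflation error and from 50 per arm matching one-sided 0.05. A reader might also infer that the unbudgeted loss falls mainly on the nonoperative arm. The Discussion does expect those patients to be in worse condition, but the odds ratios are unadjusted, no loss rate by arm is stated, and the ratio is already 3.95 at 30 days. The illustration shows that the extra loss after 3 months need not be mostly nonoperative.

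**Conclusion.** The inconsistency holds: the deciding contrast is at 6 months, the attrition allowance ends at 3 months, and the stated 80% power does not describe the deciding test. On the plan's own 60%, power at 6 months with 160 recruited is at most about 52% under the 95% interval rule, or 64% at one-sided 0.05. This assumes SD 0.30, no true difference and equal arms; unequal arms with the same total would lower it.

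The part owed to timing alone cannot be computed from the article, because no 3-to-6-month loss rate is given. A range of 6 to 12 points is a reasonable indication if 6-month loss is 65 to 70% and 250 were recruited. Loss may be heavier in the nonoperative arm, but that is an inference. The point is a real and cheaply corrected fault in the sample-size statement, secondary in size to the inflation and alpha errors beside it.

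**What to change.** Keep the 6-month contrast. In the Sample size calculation, replace the 3-month allowance with expected loss and mortality to 6 months, by arm and as a range, with the source or assumption for each rate. State the power that 160 recruited patients give at 6 months under the 95% interval rule across that range. Use N/(1 − loss) for any inflation. For orientation, 65% or 70% loss would require 286 or 334 patients to leave 50 per arm, and 360 or 420 to leave 63 per arm.

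Report the treatment contrasts at all five visits from the same generalized estimating equations model as supportive results. The planned group-by-time term already provides them.

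Moving the confirmatory contrast to 3 months would make the wording agree but would not restore power: the plan's own 60% leaves 64 patients there, about 52%. It would also give up the 6-month horizon used for follow-up and costs.

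The cost is wording and a short recalculation, with no new data. The stated power becomes less favourable, and may prompt a decision on recruitment. The change should be made before any comparison of outcomes between the groups.
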